#### **4.8.3 Procedures for participant recruitment**

First, newborns from the UCIN who meet the study's eligibility criteria will be recruited. Afterward, the mother or guardian will be approached and invited to participate, with an explanation of the study's objectives and procedures. If they agree, the participation of the newborn will be authorized by the mother or guardian through the signing of the Informed Consent Form.

#### **4.8.4 Data collection and testing procedures**

The clinical history data of the newborns will initially be recorded on a medical history form, collecting information regarding the newborn's eligibility criteria for the study. Data of both the newborn and the mothers will be obtained from medical records, nursing notes, physiotherapy records, and the child's health booklet.

The number of days from the start of the protocol until the establishment of breastfeeding will be recorded, along with the period of breastfeeding maintenance in days until hospital discharge. The continuation of exclusive breastfeeding after discharge will also be assessed at 12 weeks post-term. For these records, the mother and the multidisciplinary team will be consulted. Additionally, the daily body weight of the newborns will be recorded until the completion of the protocol, as well as the total length of hospital stay.

##### *4.8.4.1. Assessments at the UCIN*

The preterm newborns in both the experimental and control groups will be evaluated by the researcher in the NICU regarding respiratory discomfort at two time-points: I) before the

start of the protocol (experimental or control), with the baby still in the incubator/crib (Day 1); and II) after the completion of the protocol with the baby positioned in the incubator/crib (Day 15).

Physiological parameters (heart rate, respiratory rate, peripheral oxygen saturation, body temperature) and behavioral state will be assessed at three-time points daily: I) immediately before the protocol (experimental or control), with the baby still in the incubator/crib; II) 60 minutes after the start of the kangaroo position (experimental or control), while the baby remains in the position; and III) 30 minutes following, with the baby repositioned in the incubator/crib.

GMs and neuromotor screening (posture and tone) will be evaluated at two time-points: I) one day before the start of the protocol; and II) one day after the completion of the protocol.

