Therefore, interdisciplinary therapeutic measures are necessary to improve the comfort of preterm newborns (GASPARDO; LINHARES; MARTINEZ, 2005) to favor the success of breastfeeding and the motor and socio-communicative development of this population. One therapeutic measure used within the Kangaroo Method to promote the care of newborns in neonatal units is the Kangaroo Position, which provides a containment experience simulating the intrauterine environment from which the newborn has been deprived. The Kangaroo Position involves keeping the newborn in a vertical position, skin-to-skin, against the parent's chest, with the baby wearing only a diaper. Kangaroo positioning begins early and increases progressively, at the family's free choice, for as long as both parties find it enjoyable and sufficient. However, each time the baby is placed in this position, it is recommended that the baby stays for at least one hour to receive its benefits. It should be performed in a guided, safe manner and with the support of a trained healthcare team (BRASIL, 2013; 2016). The Kangaroo Position positively influences the newborn's cardiorespiratory function. The slightly inclined vertical position during Kangaroo positioning favors respiratory mechanics, increasing diaphragm efficiency and lung function, with improvements in respiratory patterns and a reduction in grunting (LUDINGTON-HOE et al., 1999), peripheral oxygen saturation (BERA et al., 2014; HUNT, 2008; LUDINGTON-HOE; FERREIRA; GOLDSTEIN, 1998; SOUKKA et al., 2014), reduction in respiratory rate (BERA et al., 2014; FOHE; KROPF; AVENARIUS, 2000), and maintenance of heart rate within normal ranges (BEGUM et al., 2008; BERA et al., 2014).

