Based on the context outlined and considering that there is insufficient evidence using a physiotherapeutic intervention protocol associated with Kangaroo Position in neonatal units, some questions arise: a) Is the combination of a physiotherapeutic protocol with Kangaroo Position more effective in improving clinical outcomes, including body weight, breastfeeding, behavioral state, length of hospital stay? b) Is the combination of a physiotherapeutic protocol with Kangaroo Position more effective in improving posture and tone, and normalizing general movements, in newborns with poor motor repertoire than Kangaroo Position alone?

Considering the evidence that early intervention (SYMINGTON; PINELLI, 2016) and Kangaroo Position (NUNES et al., 2017) improve self-regulation and the mother-infant bond, it is hypothesized that the application of the physiotherapeutic intervention protocol associated with Kangaroo Position over fifteen days in stable preterm newborns hospitalized in a neonatal unit will lead to an improvement in clinical outcomes while safely maintaining vital signs. As a consequence, and based on the beneficial effects of Kangaroo Position (SANTOS; FILHO, 2016) and early intervention (MARLOW, 2004) on body posture, muscle tone, and spontaneous movement, it is expected that these newborns will show better motor patterns immediately after the protocol, and at 12 weeks post-term, compared to control newborns.

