#### *4.8.5.1 Physiotherapeutic intervention protocol*

The physiotherapeutic intervention protocol will be applied only to the experimental group. The intervention will consist of the following handling techniques: I) Lumbosacral pumping; II) Posterior stretching; III) Cervical muscle stretching; IV) Thoraco-humeral dissociation; V) Therapeutic exercise to feel the head with the hands; and VI) Positioning in supine to allow spontaneous movements of the preterm newborn. The protocol begins with lumbosacral pumping while the newborn is in a supine position with the head slightly flexed. The therapist's right hand is positioned on the lumbosacral region, and the left hand supports the anterior pelvic region. Using the right hand's middle and ring fingers, the therapist gently pulls in a caudal direction (GONÇALVES, 2012; BUSQUET-VANDERHEYDEN, 2009); without losing pelvic retroversion, the newborn is moved to a lateral position, and posterior stretching is performed with the right hand on the sacral region and the left hand positioned under the occipital bone, performing subtle, passive traction on both sides of the vertebral axis during expiration (LIMA, 2012; BUSQUET-VANDERHEYDEN, 2009). After this handling, cervical stretching is performed with the therapist's right hand holding the shoulder and the left hand supporting the occipital and temporal regions. The newborn is raised to approximately 30°, the head and neck are gently slid to the right side, while the left shoulder is softly lowered. The shoulder is released, and the head is returned to the midline. The hands are reversed, and the movement is performed on the opposite side (DUARTE et al., 2011); immediately after this handling, thoraco-humeral dissociation is performed, where the therapist uses one hand to hold the shoulder region and makes circular movements in a postero-anterior direction (LIMA, 2012); in the exercise to feel the head with the hands, the newborn remains in a supine position, with the cervical spine straightened, trunk and lower limbs flexed, and the newborn's hands are moved to the parietal region, sliding the palms of the hands forward and laterally over the face, rubbing them in front (DUARTE et al., 2011); to finish, the newborn will be positioned in a supine position in the incubator/crib, allowing spontaneous movements with the nest slightly away. The protocol will last 15 minutes, and immediately afterward, the newborn will be placed in the kangaroo position with the mother for 60 minutes.

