#### **4.8.3 Control protocol**

The newborns in the control group will undergo the same kangaroo positioning procedures described earlier but will not receive the physiotherapy intervention protocol. Thus, the newborn will be positioned in the incubator/crib before being placed in the kangaroo position with the mother.

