## 5. Risks and Benefits

This study presents no physical or psychological risks to the newborn; however, there may be signs of sensory overload such as: color fluctuations (paleness, perioral cyanosis, among others), cardiorespiratory changes (bradycardia, irregular breathing, apnea, irregular respiratory rate), changes in state (hiccups, yawning, salivation, startles, crying, irritability), and signs of withdrawal when the newborn is handled. If signs of overload are detected, the handling should be interrupted to allow the newborn to organize, using maneuvers such as positioning and firm touch.

As for the benefits, the research will provide early stimulation/intervention to hospitalized preterm newborns, enhancing the baby's interaction with the environment through sensory-motor stimuli, which the baby interprets as pleasurable (approach signals). The kangaroo position is a safe and low-cost intervention, which can be performed in any hospital and provides the multidisciplinary team with an important additional resource in the care and attention of preterm newborns and their families, making them active participants in the treatment and promoting an efficient transition from the hospital environment to the home environment.

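### No scheduled vital-sign or behavioural reading falls during or at the end of the 15-minute handling, so its acute tolerance cannot be compared between arms

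*Protocol*

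**What the plan says.** Protocol section 4.8.4.1 lists heart rate, respiratory rate, peripheral oxygen saturation, body temperature and behavioural state for recording at three points each day:

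- Reading I: "immediately before the protocol (experimental or control), with the baby still in the incubator/crib".
- Reading II: "60 minutes after the start of the kangaroo position (experimental or control), while the baby remains in the position".
- Reading III: "30 minutes following, with the baby repositioned in the incubator/crib".

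Section 4.8.5.1 gives the order of an experimental session: "The protocol will last 15 minutes, and immediately afterward, the newborn will be placed in the kangaroo position with the mother for 60 minutes". Under the heading Control protocol (numbered 4.8.3), control infants have the same kangaroo position "but will not receive the physiotherapy intervention protocol". They lie in the incubator or crib beforehand, for a time that is not stated.

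Section 4.9.2 makes behavioural state and the physiological parameters secondary outcomes, with vital signs recorded daily before and after the protocol. The hypothesis in section 1 is that the combined intervention "will lead to an improvement in clinical outcomes while safely maintaining vital signs".

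Section 5 (Risks and Benefits) names possible signs of sensory overload, among them "cardiorespiratory changes (bradycardia, irregular breathing, apnea, irregular respiratory rate" and perioral cyanosis, and says handling is interrupted if such signs are detected. Section 4.4 excludes infants who become clinically unstable during the procedure.

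**The concern.** The trial asks what the handling adds to kangaroo position. The protocol itself expects that any adverse response may be immediate: section 5 links signs of withdrawal to the infant being handled, and section 4.4 speaks of instability during the procedure. Yet the recorded readings skip that interval. Both later readings follow an hour of kangaroo position, which both arms receive and which section 1 credits with better saturation, a lower respiratory rate and "maintenance of heart rate within normal ranges". A short-lived response to handling could have settled before anyone writes a number down.

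The exclusion rule adds to this. Only experimental infants can be excluded for reacting to handling, and neither in-session events nor interruptions are defined as an outcome. The acute reactions could therefore be missing both from the readings and from the group analysed. At stake is what the trial may claim: similar vital signs at the end of kangaroo position could be reported as evidence that the handling is well tolerated, which the data would not show. Later analysis cannot recover readings that were never taken.

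**Working it through.** The plan states no figure on this point, so there is none to reproduce. The check is a timeline for one experimental session, with minute 0 at the start of handling.

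**Inputs**

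- Handling lasts 15 minutes, and 60 minutes of kangaroo position follow without a gap (4.8.5.1).
- Reading I is immediately before the session; reading II is 60 minutes after kangaroo position starts; reading III is 30 minutes after that (4.8.4.1). I take the 30 minutes to run from reading II. If they run from the return to the crib, reading III is no earlier.
- The course is 10 days (abstract, section 3.1) or 15 days (hypothesis in section 1, and 4.8.5.2). The document gives both and they need reconciling; the result per session is the same either way.

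**Timeline**

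| Event | Minute | Minutes after handling ends |
|---|---|---|
| Reading I | 0 | before handling |
| Handling | 0 to 15 | – |
| Kangaroo position | 15 to 75 | 0 to 60 |
| Reading II | 15 + 60 = 75 | 75 − 15 = 60 |
| Reading III | 75 + 30 = 105 | 105 − 15 = 90 |

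- Readings during handling or at its end: 0 of 3.
- Handling time with no scheduled reading, per infant: 15 × 10 = 150 minutes over 10 sessions, or 15 × 15 = 225 minutes over 15.

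**Does anything else fill the gap?**

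- Section 4.9.2 asks only for vital signs before and after the protocol each day, so it adds no time point to 4.8.4.1.
- Section 4.6 lists the oximeter for heart rate and saturation but does not schedule a reading during handling.
- The Silverman-Andersen score is set for Day 1 and Day 15 in 4.8.4.1 and for each day in 4.9.2. Neither ties it to the handling.
- Sections 5 and 4.4 say what happens when signs are noticed. Neither asks for a count, or for a comparison of counts between arms.

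**Which effects the planned comparison can show**

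- An effect still present 60 or 90 minutes after handling: yes, at readings II and III.
- An effect that builds up over days: yes, through the daily readings.
- An effect present during handling or as it ends and gone within the hour: no.

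**The case against.** The strongest reply is that the protocol does watch the infant during handling. Section 5 has handling interrupted when overload appears, section 4.4 lists cyanosis, crying, lethargy and signs of pain during the procedure, and 4.8.5.2 requires signs of stress to be respected. Many of these signs are visible without an instrument, and the oximeter is routine unit equipment. This stands. A reader might infer that acute reactions cannot be seen at all, or that the interruption rule has nothing behind it; the document does not support that. What is missing is a scheduled, recorded measurement that can be compared between arms.

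The second reply is that the hypothesis concerns the combined intervention over repeated sessions, and that readings before, at the end of and after each session do test it. This also stands in part. It would be too strong to say that the safety hypothesis goes untested: lasting and cumulative effects are tested, and only the acute effect is not.

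Third, a reader might call the comparison biased toward no difference. Both arms are read at the same points relative to kangaroo position, so the schedule gives a fair contrast at those times. Leaving out an earlier time limits what is studied; it does not in itself bias what is compared. Excluding infants who react is a separate matter and could distort the comparison.

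Finally, section 5 names perioral cyanosis but not desaturation, although oxygen saturation is measured. The document gives no basis for how fast a response to handling fades, so no figure for the effect remaining at reading II can be defended.

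**Conclusion.** The point holds in a limited form. None of the three daily readings falls during or at the end of the 15-minute handling, and the first later one comes 60 minutes after it stops, once the infant has had the kangaroo position that both arms share. The acute tolerance of the one component that differs cannot be compared between arms from scheduled data, and section 4.4 may remove the infants who show a reaction. A favourable result on vital signs could be claimed for the state 60 to 90 minutes after handling, but not for the handling itself.

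The timeline rests only on the times in 4.8.4.1 and 4.8.5.1. That a response could fade within the hour is a possibility consistent with the signs the protocol names; nothing in the document shows that it happens. The point concerns secondary outcomes. Weight gain and general movements, the primary outcomes, are unaffected, so this is a cheap improvement and not a condition for the trial to proceed.

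**What to change.** - **Section 4.8.4.1:** add one daily reading of heart rate, respiratory rate, oxygen saturation and behavioural state at the end of the 15-minute handling, before kangaroo placement. Take the matched control reading after an equal 15 minutes in the crib, and state that period under Control protocol.
- **Section 4.9.2:** list this reading as the acute-tolerance time point alongside the existing ones. Report by arm the number of in-session events, interruptions and exclusions for instability, counting every randomised infant, so that infants excluded under section 4.4 remain visible in the comparison.

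The first reading after handling moves from 60 minutes to 0 minutes after it ends. Readings per infant rise from 3 to 4 a day: 3 × 10 = 30 to 4 × 10 = 40 over 10 days, or 3 × 15 = 45 to 4 × 15 = 60 over 15.

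The cost is about one extra minute per session, a short pause before kangaroo placement, a timed crib period for controls and a few more fields on the daily form. The equipment is already in use. Continuous oximetry with recording of the lowest values is not needed for this fix.

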#### *4.8.4.2. Assessments after discharge*

After hospital discharge, the GMs of babies from both groups will be assessed at 12 weeks post-term. GMA will be applied. The assessments will take place between feedings (after 1 to 1.5 hours) and should not coincide with vaccination days. The babies must be in an active alert state, i.e., state 4 (eyes open, no crying, but exhibiting gross movements) (BRAZELTON et al., 1976). The assessments will be conducted on a mat, with the baby preferably wearing only a diaper. If the baby is not cooperative, showing crying or restlessness, the assessment will be interrupted, the baby will be calmed, and the assessment will resume. If the baby remains restless, a new date will be scheduled.

The assessments will be filmed and scored later. The camera will be mounted on a tripod with sufficient distance and angle to capture the baby's full-body movements. Post-discharge assessments may take place through home visits or at the Neuropediatrics Study Laboratory (LABEN) at the Integrated School Clinic-UFMS, as per the parents'/guardians' preference. Training and agreement indices will be conducted between at least two experienced researchers/observers for assessment using the instruments, aiming for a minimum agreement index of 80%.

#### **4.8.5 Experimental protocol**

The experimental protocol will consist of a physiotherapeutic intervention protocol associated with the kangaroo position.

#### *4.8.5.1 Physiotherapeutic intervention protocol*

The physiotherapeutic intervention protocol will be applied only to the experimental group. The intervention will consist of the following handling techniques: I) Lumbosacral pumping; II) Posterior stretching; III) Cervical muscle stretching; IV) Thoraco-humeral dissociation; V) Therapeutic exercise to feel the head with the hands; and VI) Positioning in supine to allow spontaneous movements of the preterm newborn. The protocol begins with lumbosacral pumping while the newborn is in a supine position with the head slightly flexed. The therapist's right hand is positioned on the lumbosacral region, and the left hand supports the anterior pelvic region. Using the right hand's middle and ring fingers, the therapist gently pulls in a caudal direction (GONÇALVES, 2012; BUSQUET-VANDERHEYDEN, 2009); without losing pelvic retroversion, the newborn is moved to a lateral position, and posterior stretching is performed with the right hand on the sacral region and the left hand positioned under the occipital bone, performing subtle, passive traction on both sides of the vertebral axis during expiration (LIMA, 2012; BUSQUET-VANDERHEYDEN, 2009). After this handling, cervical stretching is performed with the therapist's right hand holding the shoulder and the left hand supporting the occipital and temporal regions. The newborn is raised to approximately 30°, the head and neck are gently slid to the right side, while the left shoulder is softly lowered. The shoulder is released, and the head is returned to the midline. The hands are reversed, and the movement is performed on the opposite side (DUARTE et al., 2011); immediately after this handling, thoraco-humeral dissociation is performed, where the therapist uses one hand to hold the shoulder region and makes circular movements in a postero-anterior direction (LIMA, 2012); in the exercise to feel the head with the hands, the newborn remains in a supine position, with the cervical spine straightened, trunk and lower limbs flexed, and the newborn's hands are moved to the parietal region, sliding the palms of the hands forward and laterally over the face, rubbing them in front (DUARTE et al., 2011); to finish, the newborn will be positioned in a supine position in the incubator/crib, allowing spontaneous movements with the nest slightly away. The protocol will last 15 minutes, and immediately afterward, the newborn will be placed in the kangaroo position with the mother for 60 minutes.

#### *4.8.5.2 Kangaroo Position protocol*

In the kangaroo position, the newborn should be placed only in a diaper in a vertical or elevated diagonal position, between the mother's breasts, with the head laterally positioned, upper and lower limbs in flexion and adduction. The mother should not wear a bra and should be dressed in a gown with a front opening. After positioning the baby, the mother should cover

him with the gown, and then the dyad should be secured with a moldable cotton band for additional safety (BRASIL, 2013).

The experimental protocol will begin when the baby reaches 34 weeks of postmenstrual age, has been alive for more than 72 hours, weighs over 1100g, and is clinically stable, respecting signs of stress (DUARTE et al., 2011). It will be conducted during the following 15 days. By the end of the protocol, each newborn will have received 15 sessions of the physiotherapeutic protocol combined with the kangaroo position. The interventions will be scheduled during the intervals between feeding times (oral or via tube). Stress factors such as noise and lighting will be minimized during the experimental and control protocols. The procedure will only be conducted after the newborn has been fed, waiting at least 60 minutes after feeding.

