### **Abstract**

Preterm newborns are vulnerable to perinatal conditions due to their organic immaturity and associated external factors. This association can lead to neurological impairments, affecting motor development, respiratory mechanics, and the establishment of breastfeeding. Considering the current approach to the humanization of neonatal care, as well as the recent Brazilian epidemiological need for studies focused on early intervention in hospitalized newborns at risk or with established neurological problems, the necessity for therapeutic investigations that help prevent and minimize morbidities in this population becomes evident. The primary objective of this study is to evaluate the short- and medium-term effects of a physiotherapeutic intervention protocol associated with kangaroo positioning on the neuromotor behavior and clinical outcomes of preterm newborns in a neonatal unit. A randomized controlled trial with a parallel group design and balanced distribution ratio will be conducted. A total of 34 preterm newborns, with more than 72 hours of postnatal life and stable clinical conditions, admitted to Neonatal Intermediate Care Units will participate in this study. They will be randomly divided into two groups: a) Experimental Group (EG), which will receive the physiotherapeutic intervention protocol associated with kangaroo positioning; and b) Control Group (CG), which will receive only the kangaroo position. The protocol will be implemented over 10 consecutive days, with each session of the physiotherapeutic intervention lasting 15 minutes and 60 minutes of kangaroo positioning, during the period from 34 to 36 weeks and 6 days of postmenstrual age. Primary outcomes will include weight gain at the end of the protocol; Prechtl's general movements assessment at 36 weeks postmenstrual and 12 weeks post-term. Secondary outcomes will include posture and muscle tone, behavioral state, time to establish and maintain breastfeeding, duration of hospitalization, and vital signs. This study will provide experimental support for evidence-based practice, and its results may be used to guide feasible intervention protocols for the routines of neonatal unit teams in Brazilian hospitals.

**Keywords:** Early stimulation. Kangaroo method. Preterm newborn. Child development.

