### **3 Objective**

#### **3.1 General objective**

To investigate the short- and medium-term effects of a physiotherapy intervention protocol combined with Kangaroo Positioning over ten days on the neuromotor behavior and clinical outcomes of stable preterm newborns hospitalized in a neonatal unit.

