#### **4.9.2 Secondary outcomes**

- **Posture and Muscle Tone:** behavior regarding posture and muscle tone, assessed by the classification achieved using the neurological signs evaluation method from the neonatal neuromotor screening (GONÇALVES, 2012).
- **Behavioral State:** Behavioral state according to the adapted Brazelton scale (BRAZELTON et al., 1976).

- **Time to Establish Breastfeeding:** defined as the interval in days between the start of the protocol and successful breastfeeding at the breast. Success in breastfeeding will be considered according to the main key points for proper positioning and latch during the feeding: the baby's face facing the breast, with the nose at nipple level, the baby's body close to the mother's, with the baby's head and torso aligned; the baby well supported; more areola visible above the baby's mouth; mouth wide open; lower lip turned outward; and the chin touching the breast (BRASIL, 2011a).
- **Exclusive Breastfeeding Maintenance:** defined as the continuation of exclusive breastfeeding at corrected ages of 2 weeks post-term, 12 weeks post-term, and at 6 months, being dichotomous.
- **Hospitalization Time:** defined as the average number of days the newborn stays in the hospital environment.
- **Degree of Respiratory Distress** obtained by summing the score according to the BSA (SILVERMAN; ANDERSEN, 1956; BRASIL, 2011b) on each day of the protocol.
- **Physiological Parameters** (heart rate, respiratory rate, peripheral oxygen saturation, body temperature): vital signs evaluated and recorded before and after the protocol (experimental and control) each day.

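### The protocol gives two treatment durations, 10 and 15 days, so the exposure, the end-of-protocol weight gain and the timing of the post-protocol GMA are not fixed

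*Protocol*

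**What the plan says.** **Duration.** Two places give 10 days. The abstract: "The protocol will be implemented over 10 consecutive days". Section 3.1 (general objective): "combined with Kangaroo Positioning over ten days". Three places give 15. The hypothesis at the end of section 1: "associated with Kangaroo Position over fifteen days". Section 4.8.4.1 places the closing respiratory assessment "after the completion of the protocol with the baby positioned in the incubator/crib (Day 15". Section 4.8.5.2 gives 15 days and states that "each newborn will have received 15 sessions of the physiotherapeutic protocol combined with the kangaroo position". The control protocol repeats the same kangaroo procedures, so it inherits the same uncertainty.

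**Weight gain (primary).** The abstract sets it at the end of the protocol. Sections 4.8.4 and 4.9.1 describe daily weights during the protocol and name no endpoint day.

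**Post-protocol GMA (primary).** The abstract lists "general movements assessment at 36 weeks postmenstrual and 12 weeks post-term". Section 4.8.4.1 schedules the in-hospital follow-up GMA "one day after the completion of the protocol". Section 3.2 says only that it comes after the protocol period. Section 4.9.1, which defines the primary outcomes, gives no time. The sample size in 4.2 is built on general movement quality after the intervention.

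**Respiratory score (secondary).** Section 4.8.4.1 schedules it at two time points. Section 4.9.2 defines it "on each day of the protocol".

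**The concern.** Duration settles three things: how much treatment is tested, which day counts as the end of the protocol, and when the post-protocol GMA falls. With two durations in force, the report could not say from the protocol alone what exposure had been planned, and end-of-protocol weight gain would have two meanings. The GMA has a further ambiguity, because one anchor is an age and the other is a treatment milestone. They coincide for some infants and not for others, depending on the age at which treatment begins.

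This is not detail that a protocol may leave to an analysis plan. The protocol itself states the conflicting values.

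**Working it through.** **Inputs.** Earliest start 34w0d (4.8.5.2), which other conditions in that section can delay. Window 34w0d to 36w6d (abstract). Duration L = 10 or 15 days. Follow-up GMA one day after completion (4.8.4.1). One session a day, with the first on the start day.

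**Convert to days.** 34w0d = 34 × 7 = 238. 36w0d = 252. 36w6d = 258. The window is 258 − 238 + 1 = 21 days.

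**Formulas.** Last session = start + L − 1. Day-after GMA = start + L. Latest start with all sessions inside the window = 258 − L + 1.

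| | L = 10 | L = 15 |
|---|---|---|
| Last session, start 34w0d | 238 + 9 = 247 = 35w2d | 238 + 14 = 252 = 36w0d |
| Day-after GMA, start 34w0d | 248 = 35w3d | 253 = 36w1d |
| Latest start | 249 = 35w4d | 244 = 34w6d |
| Possible start days | 249 − 238 + 1 = 12 | 244 − 238 + 1 = 7 |
| Day-after GMA, latest start | 259 = 37w0d | 259 = 37w0d |

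**When do the two GMA anchors agree?** Read 36 weeks as completed weeks, that is 36w0d to 36w6d. Agreement needs 252 ≤ start + L ≤ 258.

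- L = 10: start from 242 to 248, that is 34w4d to 35w3d. This is 7 of the 12 possible start days. The four earlier starts put the day-after GMA before 36w0d, and the one later start puts it at 37w0d.
- L = 15: start from 237 to 243. Cut at the earliest permitted start, this is 34w0d to 34w5d, or 6 of the 7 possible start days. A start at 34w6d puts the GMA at 37w0d.

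If the 15 days are counted from the day after the infant reaches 34w0d, the dates from that start move one day later (35w4d and 36w2d). The pattern is the same.

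**Size of the duration conflict.** 15 − 10 = 5 days. Five extra sessions on 10 is 50% more. The documents give no expected rate of weight gain. At an assumed 20 to 30 g/day, a 15-day gain exceeds a 10-day gain by 5 × 20 = 100 g to 5 × 30 = 150 g.

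**Sample size.** The protocol's 13 per group does not depend on the duration. The two rates behind the 50% difference are not stated. With α = 5% two-sided, 80% power and no continuity correction, assumed rates give 11 (0 vs 0.5), 12 (0.05 vs 0.55), 14 (0.1 vs 0.6) and 15 (0.25 vs 0.75). The stated 13 lies within that range and is not in question here.

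**Respiratory score.** Two scheduled readings, on Day 1 and Day 15, cannot supply a value for each day of a 10-day or 15-day protocol.

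**The case against.** The procedural sections that staff would work from, 4.8.4.1 and 4.8.5.2, both give 15. The 10-day figure appears only in the abstract and the general objective. Under the procedural text the day-after GMA from a 34w0d start is 36w1d, which is 36 weeks in completed weeks, so the GMA conflict is largely a consequence of the duration conflict. This stands in good part: with 15 days the anchors disagree for only one possible start day. It does not remove the point, because nothing in the protocol ranks the procedures above the stated objective, and one anchor still has to be chosen for later starts.

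A reader might infer several stronger things that the documents do not support.

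- *That neither primary outcome has a defined time.* The 12-week post-term GMA is stated consistently in the abstract, 3.2 and 4.8.4.2. Weight gain has a single anchor, the end of the protocol, and its day is uncertain only through the duration.
- *That the 100 to 150 g is a bias in the treatment comparison.* Both arms follow the same kangaroo schedule and allocation is randomised. The figure is a shift in the outcome scale common to both arms. A 15-day record of daily weights would also contain the day-10 weight.
- *That the two recruiting hospitals would follow different durations.* Nothing in the protocol indicates this.
- *That the assessment day ought to be counted from randomisation.* The protocol states no such anchor. Preferring it to the two already there would be a matter of taste.

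**Conclusion.** The point holds as an internal inconsistency. The protocol states both 10 and 15 days, a difference of 5 days or 50% in sessions, so the exposure tested and the meaning of end-of-protocol weight gain are not fixed. The post-protocol GMA, the assessment behind the sample size, has two anchors that agree in completed weeks only for starts from 34w4d to 35w3d (10 days) or 34w0d to 34w5d (15 days). The 12-week GMA and the 13 and 17 per group are unaffected. The respiratory score cannot be obtained as defined from the visits scheduled, which is a separate and smaller matter.

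The dates rest on one session a day starting on day 1 and on all sessions falling inside the stated age window. The weight figure rests on the assumed 20 to 30 g/day. No distortion of the between-group effect has been shown. What has been shown is that core definitions are ambiguous. They should be settled before recruitment.

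**What to change.** 1. Reconcile the abstract, the hypothesis in section 1, and sections 3.1, 4.8.4.1 and 4.8.5.2 to one duration and one session count. Which one is for the clinical team to decide.
2. In 4.9.1, state one time point for end weight. State one of the two existing anchors for the post-protocol GMA, either the postmenstrual age or the day after completion. Apply it identically in both arms, delete the other, and bring the abstract, 3.2 and 4.8.4.1 into line.
3. Make 4.8.4.1 and 4.9.2 agree on the respiratory score schedule.
4. State the latest start age that follows from the chosen duration and the age window.

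This is a wording change, with no effect on sample size. If infants have already been enrolled, the duration actually delivered should be recorded alongside the correction.
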